### Screening and Enrollment

Research assistants in our team are responsible for identifying patients from retrospective cohort and consultation outpatient in the Department of Chronic Disease Management at GPHCM to ensure they meet inclusion criteria. Considering the retrospective cohort is an observational cohort, this study will use the date when the patients are enrolled in the new cohort as their baseline time. After pre-evaluation, nurses will first make an appointment and then explain the study to candidates through a face-to-face interview and answer any questions they have. If the patients do not agree to enroll in SMP-CKD cohort, they will be registered in the chronic disease management clinic in GPHCM and do regular follow-up based on the clinic rules (as the control cohort). After confirming eligibility, all participants will sign an informed consent. (Study process can be found in Fig. 1).

**Fig. 1 Fig1:**
[figure not shown]
Details of study process

### Follow-up and Retention

After the pre-evaluation of the baseline variables, a corresponding individualized follow-up calendar will be formulated. If there are no special circumstances, visits will be conducted semiannually in stage 1–2 patients and trimonthly in stage 3–5 CKD patients. Flexibility of 1 week before or after the next visit is allowed. The timeline can be found in Table 1.

**Table 1 Tab1:**
[figure not shown]
Details about data collection

Items that all the patients should finish; Extra items that patients with CKD stage 3–5 should finish

In view of reducing the systematic attrition in this long-term cohort, some retention strategies will be considered: 1) During each visit, patients will receive a paper-version calendar for reminding their next clinic visit. 2) A week before a visit, nurses in the research team will send text messages to remind them the date for their appointment. Then, those who do not respond to the text messages will be contacted again within 3 days. 3) A final notice will be sent to patients via social media apps-WeChat, a very popular communication tool in China to keep them informed of the appointment. 4) Gift/ freebies incentives for finishing a one-year follow-up circle.

Self-management intervention design and process evaluation.

### Intervention design

Social Cognition Theory (SCT) will be applied to design a theory-based complex intervention. According to SCT, motivational enhancements can ultimately lead to behavior modification. It can help the individual modify their behaviors, and then elevate the individual’s perceived self-efficacy and outcome expectations [30]. The Behavior Change Technique Taxonomy v1 will be used to specify the self-management intervention functions and behavior change techniques [31].

Self-management interventions components will be selected by reviewing existing epidemiological evidence, consulting clinical psychologists, sociologist, epidemiologists, and holding group meetings. The components of this complex intervention include education, nutrition/diet modification, lifestyle change recommendation, medication review and psychology support. A multidisciplinary team consisting of nephrologists, nurses, dietitians, and postgraduate students will be in charge of the delivery of all the interventions. All the team members will participate in a 1-day workshop to standardize their delivery.

The education will entail a 1.5-h integrated slide-lecture, delivered by nephrologists and dietitians trimonthly involving general CKD knowledge, dietary management, healthy lifestyle, pharmacological regimens and Chinese herbal medicine instructions. Cooking courses will be offered semiannually for 2 h a session with different topics (macro-and micro-nutrients intake and restriction, label reading, eating out, et al.), provided by dietitians and nurses. All the courses will be taught in Cantonese or Mandarin to accommodate the main languages spoken in the Guangdong Province.

After assessing baseline anthropometric parameters and biochemical findings, patients will receive face-to-face dietary counseling from a dietitian includes the protein, caloric, potassium, phosphorus, sodium intake recommendations. Before each follow-up/clinic visit, they will be asked to fill a diet diary to record all foods and beverages consumed for 72 h, in succession two weekdays and one weekend day, then dietitian will assess their compliance by analyzing the diary data and offer new individualized dietary prescriptions. All these recommendations and prescriptions are based on the Chinese guideline [32].

During each visit, assessments include questionaries review of CKD knowledge, symptoms, comorbidities, lifestyle change (physical activity attendance, smoking status, alcohol intake), psychological and self-efficacy status by postgraduate students and nurses will be carried out. Then nephrologist will hold a 30-min one-on-one, face-to-face individualized interview based on current self-management practices and biochemical markers. The content of the interview will cover medication review, knowledge gain, thoughts and feelings, using an interactive, psychosocial approach underpinned by the SCT.

Some behavior change techniques will be used in this study, they can be grouped into 5 domains: goals and planning, feedback and monitoring, social support, self-belief and shaping knowledge. On the goals and planning domain, the research team set some individualized goals in terms of the behavior to be achieved (e.g., daily walking at least 60 min), or a goal for a positive outcome at the beginning of the study. In the next follow-up, we will review behavior goals jointly with patients and consider modifying goals in light of their achievement. In the feedback and monitoring domain, self-monitoring of behavior will be adopted (e.g., 3-day food diary), then the research team monitor and provide evaluative feedback on the performance of patients’ behavior (e.g., check how many nutrients they intake each day by analyzing their food diary) or biofeedback (e.g., inform their blood pressure or eGFR slope curve). The techniques of instruction on how to perform a behavior and information about antecedents will be applied to the shaping knowledge domain. For example, when conducting nutrition-related lectures, food models will be displayed. Both practical and emotional social support will be used in this study, verbal persuasion about capability and mental rehearsal of successful performance techniques will be used to boost self-efficacy.

Medical staff, patients and their caregivers are included in the intervention to facilitate their behavior change. To encourage a collaborative patient role, the research team will encourage patients to report problems directly to team members whenever they raise questions, through face-to-face, telephone and WeChat apps. Details are shown in Table 2 logic model for self-management in CKD.

**Table 2 Tab2:**
[figure not shown]
Logic Model for Self-management in CKD

### Process evaluation

There are 3 aims of this process evaluation (1) program fidelity between the planned and actual implementation of the intervention (2) self-management adherence rate (3) contextual factors influencing and maintaining user engagement with the intervention. The details are shown in Table 3.

**Table 3 Tab3:** Process Evaluation components and Definition

Components	Definition	Data source
Program fidelity		
Reach	Proportion of intended target patients participate in the intervention	Delivery records
Dose delivered	The amount of the intervention components provided to patients	Delivery records, Audio records
Dose received	What extent participants actively engaged with and/or used the materials provided to them	Delivery records, Cognitive questionnaire
Duration	How long the patients participate in the intervention	Delivery records
Contextual factors	Explore contextual factors affecting patients’ engagement in the intervention	Patient survey Patient characteristics SSRS, GSES, PDRQ scale
Adherence	Self-management intervention adherence rate of the patients	Delivery records Self-management behavior questionnaire Diet diary review

An independent nurse team will be responsible for process evaluation, including data collection and management. This process evaluation team will design the process evaluation program, conduct the evaluation, and monitor its implementation. The process evaluation data will be analyzed before analyzing the cohort data.

Note: SSRS, Social Support Rating Scale; GSES, General Self-Efficacy Scale; DPRQ, Patient-Doctor Relationship Questionnaire.

## Measures

### Exposure measures

The details of the data collection are shown in Table 1. Social-demographic and clinical data will be collected only in prospective cohort by a predetermined questionnaire during the initial visit. Physical examination and laboratory markers will be collected trimonthly in patients with CKD 3–5 and semiannually in patients with CKD 1–2.

The nutritional parameters will be evaluated by 1) a validated daily diet record form recording all foods and beverages consumed for 72 h, in succession two weekdays and one weekend day before the 24-h urine sample is collected. Trained staff will teach all patients how to keep proper records in their diet logs. These dietary data will be converted into daily nutrient intakes by using the “Chinese food composition list, 2nd edition” [33]. 2) Inbody-770 and tool measuring for anthropometric parameters and Medgraphics Ultima CCM for metabolic characteristics [34, 35]. 3) Patient-Generated Subjective Global Assessment (PG-SGA) for symptoms, metabolic stress and nutritional status [36].

A 11-item self-management behavior questionnaire developed by our team will be used to measure the self-management compliance. Patients-reported outcomes (PROMs) will be used to identify lifestyle factors, self-efficacy, psychological status and quality of life. A cognitive questionnaire will be given to determine patients’ cognitive levels so that the nursing group can schedule receptive and individualized courses [37]. Social support score will be collected by the Social Support Rating Scale (SSRS), self-efficacy score will be assessed by General Self-Efficacy Scale (GSES), and patient and doctor relationship will be measured by a developed Patient-Doctor Relationship Questionnaire (PDRQ-13) [38–40]. Patients’ other lifestyle factors (e.g., sleep and physical activity) will be evaluated by the Pittsburgh Sleep Quality Index (PSQI), and the International Physical Activity Questionnaire (IPAQ) [41, 42]. The Short Form Healthy Survey Questionnaire (SF-12) will be used to measure CKD patients’ quality of life [43]. All above self-reported questionnaires are validated in Chinese population.

### Outcome measures

The primary outcome is the occurrence of composite clinical endpoints (doubling of serum creatinine level, ESKD(eGFR < 15 ml/min for CKD 1–4 patients; or dialysis for at least 30 days or kidney transplant for patients with CKD 1–5), loss of renal function(≥ 40% decline in GFR from baseline), death(from any cause), major cardiovascular or cerebrovascular events) during the 5-year follow up (shown in Table 4) [44, 45]. Those outcome data will be collected through the outcome assessment scale during each visit by reviewing the laboratory test results and the medical record in Hospital Information System (HIS).

**Table 4 Tab4:** Definition of composite clinical endpoints

Clinical events	Definition
1.A doubling of serum creatinine levels	Doubling of the serum creatinine level from baseline sustained for at least 30 days according to central laboratory assessment
2.End-stage kidney disease (ESKD)	eGFR < 15 ml/min for CKD 1–4 patients; or dialysis or kidney transplant for CKD 1–5 patients
3.Loss of renal function	≥ 40% decline in GFR from baseline
4.Death	Death from any cause
5.Major cardiovascular or cerebrovascular events	Acute heart failure, myocardial infarction, ischemic cerebral infarction or intracranial hemorrhage

The main secondary outcomes include the absolute change and slope of eGFR, absolute changes of urinary protein creatinine ratio, 24-h urine proteinuria, intact parathyroid hormone level (iPTH), and self-management adherence rates (evaluated by self-management behavior questionnaire) and quality of life. Other outcomes include serum creatinine level (SCr), blood urea nitrogen level (BUN), plasma albumin, triglyceride, cholesterol, calcium, phosphate and other Laboratory markers and cardiovascular function.

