## Methods

### Study design and study population

An ambispective cohort study will be conducted in the department of nephrology at the three branches of Guangdong Provincial Hospital of Chinese Medicine (GPHCM) in Guangdong province, China. Two branches are located in different Districts in Guangzhou city (Yuexiu and Fangcun District) and one in Zhuhai city. The study population includes all CKD 1–5 patients (speak Cantonese or Mandarin) attending the CKD consultation outpatient clinic in GPHCM from July 2015 to July 2024. Of 200 CKD patients were already registered in the retrospective cohort from July 2015 to July 2019 and they will keep following in the prospective cohort. Beginning in August 2019, a prospective cohort will be built on. All the patients will be followed for at least 5 years, or until the occurrence of a primary outcome.

CKD is defined by a glomerular filtration rate (GFR) < 60 mL/min/1.73 m2 or markers of kidney damage, or both, of at least 3 months duration [5]. GFR is calculated by CKD-EPI equation, and CKD staging will use the Kidney Disease Outcomes Quality Initiative (KDOQI) definition [29]. Patients are eligible for inclusion if they are Chinese, aged 18 to 80 years, have CKD (Stages 1–5), and give a written signed informed consent. Exclusion criteria for the study are psychosis or unable to cooperate with clinical staff for other reasons and have a history of dialysis or renal transplant.

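### The 30-day persistence rule covers creatinine doubling but neither eGFR criterion, so a transient doubling enters the primary composite as a 40% decline

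*Protocol article*

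**What the plan says.** The composite is defined in the Outcome measures section, in the text and in Table 4.

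- Creatinine (Table 4): "Doubling of the serum creatinine level from baseline sustained for at least 30 days according to central laboratory assessment".
- Loss of renal function (text and Table 4): at least a "40% decline in GFR from baseline", with no duration, repeat test or central-laboratory condition.
- ESKD (Table 4): "eGFR < 15 ml/min for CKD 1–4 patients; or dialysis or kidney transplant for CKD 1–5 patients". The text words the dialysis limb differently: "dialysis for at least 30 days or kidney transplant for patients with CKD 1–5". Neither place attaches a duration to the eGFR limb.

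Under Study design and study population, "GFR is calculated by CKD-EPI equation". Under Follow-up and Retention, "visits will be conducted semiannually in stage 1–2 patients and trimonthly in stage 3–5 CKD patients". Events are collected at each visit from laboratory results and the hospital record, and no confirmatory sample is mentioned. Patients are followed for 5 years or until a primary outcome occurs.

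**The concern.** The plan asks for persistence on the more extreme creatinine-based criterion and not on the milder one derived from the same measurement. If the milder criterion is met whenever the more extreme one is, the persistence rule keeps almost nothing out of the composite. Measurement noise or a passing rise in creatinine could then be recorded as a primary event.

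Three things are at stake. False events feed the chi-squared, log-rank and Cox analyses and, if they are equally likely in both cohorts, pull the hazard ratio towards 1. They become more frequent with more tests, and the schedule gives about 20 tests over 5 years in stages 3–5 against about 10 in stages 1–2, which matters for the planned subgroups by baseline eGFR. A false event can also end that patient's observation, so that later true events are lost.

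**Working it through.** **1. Does doubling imply a 40% fall?** Let eGFR vary as creatinine to the power −b. The protocol names CKD-EPI but does not print its exponents, so b is an assumption. A doubling lowers eGFR by 1 − 2^(−b), and a 40% fall is reached at a creatinine ratio of 0.6^(−1/b).

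| b (assumed) | eGFR fall at doubling | Creatinine ratio giving a 40% fall |
|---|---|---|
| 0.8 | 43% | 1.89 |
| 1.0 | 50% | 1.67 |
| 1.2 | 57% | 1.53 |

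Doubling implies at least a 40% fall whenever b ≥ ln(1/0.6)/ln 2 = 0.737. The exception is a very low baseline creatinine, if the equation is much flatter there. With assumed low-range exponents of 0.33–0.41, doubling fails to reach 40% only from a baseline below about 0.6 mg/dL (men) or 0.48 mg/dL (women). This step needs no assumption about measurement error.

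**2. How often would a single value mislead on the 40% criterion?** Simulation of 200,000 patients per scenario: baseline eGFR 45, linear loss, independent log-normal error on the baseline and on each of 20 quarterly values. The CV of 8–10% is an assumption. The true fall over 5 years is 0% with no loss, 10/45 = 22% at 2 per year and 15/45 = 33% at 3 per year. None reaches 40%, so every declared event is false.

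| Loss per year | Any single value | Two consecutive values |
|---|---|---|
| 0 | 0–0.3% | about 0% |
| 2 | 3–10% | 0–1% |
| 3 | 31–42% | 8–14% |

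With 10 tests instead of 20, the 42% (loss 3 per year, CV 10%) becomes 33%. Over a wider range of CV (8, 12, 15, 20%), with no true decline and 20 tests, the single-value rate is 0.0, 1.9, 8.8 and 27.0%, against 0.0, 0.1, 1.0 and 6.1% for two consecutive values.

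**3. The eGFR below 15 limb.** Stable true eGFR, four quarterly tests in one year, assumed CV 5–10%:

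| True eGFR | Any value below 15 |
|---|---|
| 16 | 34–70% |
| 17 | 2–36% |
| 18 | 0.05–13% |
| 20 | 0–0.8% |
| 25 | 0% |

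Requiring two consecutive values gives 3–17% at 16 and 0–3% at 17. The problem is confined to stage 4 patients at about 15–18.

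**4. Effect on the comparison.** With assumed mean losses of 1.9 against 2.5 per year (SD 2.5), baseline 45 and CV 8–10%, the hazard ratio is 0.72–0.74 on single values and 0.70–0.72 when confirmed. With baselines spread over 20–90 it is 0.75–0.77 against 0.74–0.75. The shift is about 0.01–0.02. At CV 15% it is about 0.04–0.05 (for example 0.78 against 0.73).

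**5. The plan's event target.** 30 variables × 10 events = 300, as stated. The assumed rate gives 0.06 × 1,200 × 5 = 360 events on full person-time, or 1,200 × (1 − e^(−0.3)) = 311 if each patient stops at a first event, before losses. No component rates are given, so the number of these events that confirmation would remove cannot be computed.

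**The case against.** The strongest reply is that the effect on the treatment comparison is small. At a CV of 8–10% the hazard ratio barely moves, and because unconfirmed events are more numerous, power is no worse without confirmation. That stands, and it limits the severity. The simulations cover measurement noise only. Acute transient illness is not modelled.

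The large percentages also belong to patients near a threshold. The 31–42% needs a true fall of 33%, and in that scenario the false events come at a median of 4.25 to 4.5 years, so they are mostly early calls in patients who really are progressing. A reader might infer that a third of the cohort would have false events. The documents do not support this, since they do not give the distribution of baseline eGFR or of slopes.

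Three other stronger readings should be set aside.

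- That creatinine doubling alone carries a persistence rule: the text also puts 30 days on dialysis, although Table 4 drops it.
- That the plan declares one value sufficient: it is silent. A single value qualifies on the definitions as written, and the silence is not mere condensation, because the same table states persistence for one component and not for the others.
- That one cohort is tested more often and so looks worse: visit frequency is set by CKD stage, and the clinic rules that govern the control cohort give no frequency in the article.

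Finally, confirmation does not cure a noisy single baseline. At a loss of 3 per year, 8–14% false events remain, against 0.6–2.2% if the baseline were free of error.

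**Conclusion.** The concern holds as a should-fix. The structural point is firm: for nearly all patients, a doubling that fails the 30-day rule is still a primary event through the 40% criterion. It rests only on eGFR falling with creatinine at an exponent of at least 0.737 over the relevant range.

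The frequency is not firm. It depends on the assumed CV and on how many patients lie near a threshold, and ranges from negligible in stable patients to about a third or more in those truly approaching a 40% loss or sitting just above 15. The likely dilution of the hazard ratio is small under the assumed slopes, so the case for change rests on a coherent primary endpoint and on not ending follow-up for a transient value. Separately, the text and Table 4 contradict each other on whether dialysis must last 30 days.

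**What to change.** Apply the existing 30-day persistence rule to the 40% decline and to eGFR below 15. Count the event when a second value at least 30 days later, which may be the next scheduled visit, still meets the criterion, and date it at the first value. A decline followed by death or another component before the repeat counts through that component. Report the analysis with unconfirmed events as a sensitivity analysis. Reconcile the text and Table 4 on the duration of dialysis in the ESKD definition, so that one definition applies throughout.

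The cost is a change of endpoint wording, and confirmation can use visits already planned. There are three drawbacks. Fewer events count towards the 300. If only scheduled visits are used, the confirmation interval is about 3 months in stages 3–5 and 6 months in stages 1–2. A decline first seen at the last visit needs one repeat test or is not counted.

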## Sample size calculation

We selected the occurrence of composite endpoints as the primary study outcomes to calculate the sample size. Previous studies have reported that the composite endpoints rate range from 18.1–126/1,000 person-years [46, 47]. Based on these studies and our previous data, we estimated that the incidence rate of a composite endpoint in our cohort would be 60/1,000 person-years. There are about 30 variables that may affect prognosis, and there should be at least 10 endpoints per variable. Thus, we anticipate that recruiting 1,200 participants with 300 events over a 5-year follow-up will ensure adequate statistical power.

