**Methods:**

In this ambispective intervention cohort study,1,200 patients with CKD stages 1–5 will be recruited from July 2015 to July 2024 in 3 branches of Guangdong Provincial Hospital of Chinese Medicine (GPHCM) in Guangdong province, China. The patients in the self-management cohort will choose to receive an intervention that consists of education, nutrition/diet modification, lifestyle change recommendation, medication review, and psychology support based on Social Cognition Theory (SCT). The patients in the control cohort will do regular follow-ups based on the clinic rules. All the patients will be followed up for 5 years, or until the occurrence of a primary outcome. Detailed clinical, laboratory markers, nutritional status, psychological exposures and outcome questionaries will be collected semiannually in CKD stage 1–2 and trimonthly in stage 3–5 patients. The primary outcome is the occurrence of composite clinical endpoints (doubling of serum creatinine level, ESKD, loss of renal function (≥ 40% decline in GFR from baseline), death, major cardiovascular or cerebrovascular events). The main secondary outcomes include the absolute change and slope of eGFR, absolute changes of urinary protein creatinine ratio, 24-h urine proteinuria, intact parathyroid hormone level, and self-management adherence rate and quality of life from baseline to end of the study. The effectiveness of self-management will be analyzed and the association between longitudinal trajectories of self-management and renal outcomes will be evaluated.

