## Statistical analysis plan

Categorical demographic and other baseline characteristics variables will be summarized by frequencies and percentages. Continuous variables will be summarized by both mean and standard deviation for data with normal distributions or median and inter-quartile range for non-normally distributed data. Either a Chi-square or Fisher’s exact test will be used to compare categorical variables between groups, while Mann–Whitney U-test or Student’s t-test will be used for continuous variables, if necessary.

The primary objective of this cohort is to evaluate the effectiveness of the self-management program, we plan to perform three separate analyses for the primary outcome. First, the incidence rate of composite endpoint events will be analyzed by the Chi-squared test. Second, time to occurrence of composite clinical endpoints will be analyzed using log rank test. The hazard ratio (HR) with 95% CI will be estimated by using the Cox proportional hazards model or competitive risk model. Third, growth mixture models and group-based trajectory models (GBTM) will be used to analyze the trajectories of exposure and outcome variables [48]. Covariates for the models will be selected based on prior knowledge and published papers. Logistic regression or Poisson regression will be used to analyze categorical outcomes. Liner mixed-effect model will be applied to the longitudinal data, such as the absolute change, and slope of eGFR and other secondary outcomes.

Even with some retention strategies, considerable missing data is expected over 5-years follow-up. The proportion of missing data will be summarized in each group and at each visit point. If there is less than 20% of data missing for the covariate data, we will perform a complete case analysis. If there is more than 20% of missing data, we will perform Little’s test and use multiple imputations under the assumption of missing is at random. Subgroup analyses will be conducted across baseline eGFR levels, demographic status and other factors, if possible. To test the credibility and robustness of the findings, several sensitivity analyses will be performed, including E-value and other advanced models [49]. Effect modification will be investigated using stratified analyses and formal tests of interaction. Mediation will be analyzed by adding the hypothesized mediators, one by one, to the confounder-adjusted models to study the extent to which they explain any association found.

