Since self-management is a complex intervention, how to deliver a reasonable self-management intervention is still being explored [60]. We use process evaluation to provide novel information and understanding about how self-management works in clinical practice. Process evaluation will evaluate the components of execution, the influence mechanism and context to identify and understand the core components of self-management [61]. This not only can increase understanding of how the process is delivered, but also help us derive more reliable conclusions about the effectiveness of interventions in terms of whether they can be accepted by patients and healthcare professionals [62].

However, this study has some limitations. Firstly, potential selection bias or confounder effect may exist because it is a hospital-based design study, the results may not sufficiently generalize to other populations. But we try to select 3 branches hospitals, while the source populations of these three hospitals have different demographic and socioeconomic characteristics, it can increase the confidence in the generalizability of the study. And more so than other cohorts, its hospital-based design can ascertain that CKD patients’ diagnoses and the interpretations of the renal outcomes are accurate which means the risk of misclassification bias is low [63]. Secondly, the long study period is a double-edged sword. Although a considerable amount of follow-up data can be obtained during the study which allows us to have the possibilities to dynamically evaluate patients’ condition and study the relationship among longitudinal trajectories of exposure, surrogate markers, and renal outcomes [48]. High rates of patient's lost-to-follow-up are inevitable, how to minimize the drop-outs and deal with the missing data is a big challenge. One solution is the patients enrolled in this cohort are registered in the chronic disease management clinic in GPHCM, they will return to the outpatient clinic for regular checkups because we are the designated hospital for patients' medical insurance. The other solution is some retention strategies have been adopted, such as reducing barriers to participation, setting reminder strategies and gift/freebies incentives.

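### The sample size paragraph infers adequate power from an events-per-variable rule, and its 300 events hold only with near-complete follow-up

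*Protocol article*

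**What the plan says.** The Sample size calculation section cites earlier studies in which "the composite endpoints rate range from 18.1–126/1,000 person-years" and then settles on one rate: "we estimated that the incidence rate of a composite endpoint in our cohort would be 60/1,000 person-years". It takes the number of events from a modelling rule: "There are about 30 variables that may affect prognosis, and there should be at least 10 endpoints per variable". From these it concludes: "Thus, we anticipate that recruiting 1,200 participants with 300 events over a 5-year follow-up will ensure adequate statistical power".

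The abstract's Methods define the observation period: "All the patients will be followed up for 5 years, or until the occurrence of a primary outcome". The study design section of the main Methods instead makes five years a minimum.

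On attrition, the Discussion says that high rates of patients "lost-to-follow-up are inevitable, how to minimize the drop-outs and deal with the missing data is a big challenge". The Statistical analysis plan section adds that, despite the retention measures, "considerable missing data is expected over 5-years follow-up".

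The same section makes effectiveness of the programme the primary objective. The primary outcome is to be analysed with a chi-squared test, a log-rank test and a Cox or competing-risk model. Patients choose whether to join the programme, and those who decline form the control cohort.

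**The concern.** There are two separate problems.

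- **The inference.** Ten events per variable protects a multivariable model against unstable coefficients. It uses no effect size, cohort split, significance level or power. It therefore cannot show that a comparison of two cohorts has adequate power, yet the paragraph presents power as its consequence. Because patients select their own cohort, the split is not controlled, and the split bears directly on power.
- **The yield.** The 300 events are attached to 1,200 recruited patients with no visible allowance for loss, while the same article expects high loss.

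At stake is how a null result is read. A reader could take it as coming from a study known to be adequately powered, although the article never says which effect the study could detect. A smaller point is that loss would push the number of events below the article's own ten-per-variable target.

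**Working it through.** **Inputs from the article:** N = 1,200; event rate h = 0.06 per year; cited range 0.0181 to 0.126 per year; follow-up of 5 years ending at the first primary event; about 30 variables at 10 events each.

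**Assumptions, because the article gives no figure:** the loss rate, the cohort split, two-sided 5% significance (consistent with the planned 95% confidence interval), 80% power, and that the 1,200 covers both cohorts.

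**1. The article's target.** 30 × 10 = 300 events. This reproduces exactly.

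**2. Yield with complete follow-up.** The 5-year risk is 1 − exp(−0.06 × 5) = 0.2592, and 1,200 × 0.2592 = 311 events. Reaching 300 needs 300 / 0.2592 = 1,158 patients. So 300 is correct if follow-up is complete, with a margin of 11 events. The crude product 1,200 × 0.06 × 5 = 360 counts 6,000 person-years. Only about 311 / 0.06 = 5,184 are available when observation stops at the event.

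**3. Loss that uses up the margin.**
- All loss at baseline: 1 − 300/311 = 3.5%.
- Loss at a constant rate d per year: events = N × h/(h + d) × (1 − exp(−5(h + d))). This equals 300 at d = 0.0153, and 1 − exp(−5 × 0.0153) = 7.4% cumulative.

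**4. Events under assumed cumulative loss L,** with d = −ln(1 − L)/5:

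| L over 5 years | d per year | Events, loss spread evenly | Events per variable (÷ 30) | Events, all loss at baseline |
|---|---|---|---|---|
| 0% | 0 | 311 | 10.4 | 311 |
| 10% | 0.0211 | 296 | 9.9 | 280 |
| 20% | 0.0446 | 280 | 9.3 | 249 |
| 30% | 0.0713 | 264 | 8.8 | 218 |

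**5. Cited rate range, no loss.** At 0.0181: 1,200 × (1 − exp(−0.0905)) = 104 events. At 0.126: 1,200 × (1 − exp(−0.63)) = 561 events. The rate matters more than the loss, in both directions.

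**6. What the events can detect.** By Schoenfeld's formula, HR = exp(−(1.960 + 0.842)/√(D·p(1 − p))), where D is the number of events and p the share of patients in one cohort.
- D = 300, p = 0.5: exp(−2.802/√75) = 0.72.
- D = 300, p = 0.25: exp(−2.802/√56.25) = 0.69.
- D = 280, p = 0.5: exp(−2.802/√70) = 0.715, against 0.724 with 300 events.
- D = 280, p = 0.25: exp(−2.802/√52.5) = 0.679, against 0.688 with 300 events.

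These are before confounder adjustment. If confounders explained 20% of the variation in cohort membership, D would be multiplied by 0.8, and the p = 0.25 figure with 300 events becomes 0.66. With 300 events and an even split, power is 87% for HR 0.70, 70% for HR 0.75 and 49% for HR 0.80.

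**The case against.** The strongest reply is that no stated number is wrong and no shortage of power is demonstrated. Much of this stands.

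- **Arithmetic.** The target reproduces, and 311 events cover it under complete follow-up. A reader might infer a calculation error; the article does not support that. The fault is the condition left unstated.
- **Hidden allowance.** The crude method gives 300/(0.06 × 5) = 1,000 patients, and 1,200 is 1,000 × 1.2. A 20% inflation is therefore conceivable. No such step is stated, though, and the crude method ignores that observation ends at the event.
- **Longer follow-up.** The study design section makes five years a minimum. As an illustration, uniform entry over 5 years with a common close 5 years after the last entry gives 1,200 × (1 − (exp(−0.30) − exp(−0.60))/0.30) = 432 events without loss, and about 371 at d = 0.0446. This would remove the shortfall. However, the sample size paragraph and the outcome definition both count 5 years.
- **Loss.** Missing covariates or visits are not lost endpoints, so the analysis section's remark on missing data is weaker support than the Discussion's. Endpoints are also drawn from hospital records, and the article describes retention measures and the hospital's insurance role. All of this may keep loss low, but no rate is given.
- **Condensation.** A journal article may leave significance level, effect size and split to a fuller document, and their absence alone is no finding. The printed inference from events per variable to power is a different matter, and a fuller document would not make that sentence correct.

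A reader might also infer that the study is underpowered. The article does not support this: with an even split, 300 events give 87% power for HR 0.70.

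**Conclusion.** The point holds at moderate severity. The claim of adequate power does not follow from the rule offered for it; this part needs no assumption about loss or split. The 300-event figure is right only if cumulative loss stays below about 7% when evenly spread, or 3.5% when it occurs at baseline, and the Discussion expects high loss.

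The size is modest. At assumed evenly spread losses of 10% to 20%, the shortfall against 300 is 4 to 20 events, and the detectable hazard ratio moves by about 0.01. Uncertainty in the event rate is much larger, with 104 to 561 events over the cited range, and it runs both ways. Whether power is adequate cannot be judged from the article, because it names neither the effect of interest nor the expected split.

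**What to change.** Rewrite the sample size paragraph to:

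- state an assumed loss rate and the expected events net of it, for example about 280 at 20% cumulative loss spread evenly;
- state the assumed split between the self-management and control cohorts;
- give the hazard ratio detectable with 80% power at two-sided 5% under that split, noting the effect of confounder adjustment;
- present ten events per variable as a limit on model parameters, set at net events divided by ten (about 28 at 20% loss);
- replace the unqualified power claim with the detectable effect;
- say over which period events are counted, reconciling the fixed five years of the abstract, outcome definition and sample size paragraph with the five-year minimum in the study design section.

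The cost is one reworded paragraph and a slightly less favourable stated figure. It needs no additional patients.
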